10.1 Handling and storage of data and documents [14](#__RefHeading___Toc270680847)

10.2 Amendments [14](#__RefHeading___Toc270680848)

10.3 Annual progress report [15](#__RefHeading___Toc270680849)

10.4 End of study report [15](#__RefHeading___Toc270680850)

10.5 Public disclosure and publication policy [15](#__RefHeading___Toc270680851)

11. REFERENCES [15](#__RefHeading___Toc270680852)

**Summary:** Astaxanthin has been shown to be a powerful anti-oxidant. Health benefits have been shown in animals and humans. Exercise enhancing effects have been shown in animals via enhancement of fat oxidation. We want to examine the effects of 4 weeks of astaxanthin supplementation on fat oxidation and cycling performance in trained cyclists.

**Rationale:** The aim of this proposal is to investigate the effect of 4 weeks supplementation with astaxanthin on fat oxidation during exercise and exercise performance.

**Objective**: To test the hypothesis that 4 weeks supplementation with astaxanthin will improve fat oxidation and improve exercise performance in trained cyclists.

**Study design:** Double blind, placebo controlled study.

**Study population:** Well trained cyclists between 18-30 years old.

**Intervention:** astaxanthin (20 mg/day) or placebo for 4 weeks

**Main study parameters/endpoints:** The primary endpoint will be performance on a time trial after 60 min steady state exercise. Secondary endpoint will be fat-oxidation during the 90 minutes steady state 60% Wmax exercise.

**Nature and extent of the burden and risks associated with participation, benefit and group relatedness:** The risks involved in participating in this experiment are minimal. Astaxanthin has been shown to be safe. Insertion of the catheters in a vein is comparable to a normal blood draw and the only risk is of a small local haematoma.

# INTRODUCTION AND RATIONALE

The two major substrates of energy production are fat and carbohydrate. A mixture of the two substrates is being used by muscle tissue during exercise [1, 2]. The ratio between the use of fat and carbohydrate depends on exercise intensity, endogenous carbohydrate availability, training status, diet and genotype [3]. One of the main limiting factors for endurance exercise performance capacity is the availability of muscle glycogen. By enhancing fat oxidation in favor of glycogen oxidation, muscle glycogen can be spared. Consequently, stimulating fat oxidation is the main interventional strategy to improve endurance exercise performance.

Astaxanthin is a carotenoid with high anti-oxidant properties. Astaxanthin is a naturally occurring substance, synthesized by the microalgae *Haematococcus pluvialis*. Several clinical studies have found beneficial effects of astaxanthin in humans [4-7], which has been attributed to its anti-oxidant and anti-inflammatory properties. The effective doses in these human studies were 16 mg/day [4], 40 mg/day [5], 8 mg/day [6], and 12 and 18 mg/day[7]. Few studies have used different doses of astaxanthin. The studies that have used different doses in general found more effect in higher doses. Iwamoto et al. provided doses of 1.8, 3.6, 14.4 and 21.6 mag/day and the highest LDL-oxidation lag times were found in the two highest doses [8]. Yoshida et al. provided 0, 6, 12 and 18 mg/day and found the highest changes in adiponectin and triglycerides in two highest doses [7] Kupcikinas et al. found a significant reduction in reflux syndrome in 40 mg/day compared to 16 mg/day and 0 mg/day [5]. Furthermore, animal studies have shown promising results on endurance performance as well. Aoi et al. examined muscle damage after exercise in mice and found a protective effect of astaxanthin [9]. Ikeuchi et al. found a performance enhancing effect during a 5 week supplementation protocol. They measured performance every week and saw a gradual increase in performance over time and a dose response relationship, with the highest time to exhaustion found in the mice supplemented with the highest dose of astaxanthin [10]. In an attempt to explain the previous findings, Aoi et al. investigated lipid metabolism during exercise and carnitine palmityol transferase I (CPT I), a rate limiting step in fat oxidation. An increased fat oxidation during exercise was found. Furthermore, a possible mechanism to explain their findings was found. In the astaxanthin group, less modification of CPT I occurred. The authors concluded that astaxanthin protects CPT I from oxidative stress, and hence increases the capacity to transport fatty acids over the mitochondrial membrane, facilitating lipid oxidation.

As a consequence astaxanthin is now widely used in nutritional supplements to enhance exercise performance and also in nutritional supplements to support weight loss. However, so far the impact of astaxanthin supplementation on skeletal muscle substrate use and endurance type exercise performance has not been studied in humans. The present study aims to investigate the effects of 4 week astaxanthin supplementation on measures of performance and substrate utilization in healthy, well-trained endurance athletes.

# OBJECTIVES

Primary objective of this study is to test the hypothesis that 4 week supplementation of astaxanthin will improve exercise performance. Therefore, the primary endpoint will be performance on a time trial. Secondary endpoints are fat oxidation at rest and during submaximal exercise.

# STUDY DESIGN

### Protocol

An outline of the study and the exercise protocol is provided in Figure 1. Subjects will be randomized to a 4-wk supplementation protocol (astaxanthine or placebo) and an exercise performance test will be done before and after the 4-wk intervention. For the exercise performance test, subjects will report to the laboratory at 8.00 h. Resting metabolic rate will be measured by ventilated hood connected to the OmniCal IV for indirect calorimetry and substrate use measurement. Before testing, participants will be weighed, fitted with a heart-rate monitor, and familiarized with the Borg scale of perceived exertion [11]. A Teflon catheter will be inserted in an antecubital vein.

The exercise protocol consists of 60 minutes steady state exercise at 50% Wmax (as determined in trial 1, see paragraph 6.3: pretesting). Subsequently, a time-trial of about an hour will be conducted. This type of time-trial has been validated and used before in our lab[12], see for an overview of validation studies Currell and Jeukendrup [13]. Examples of coefficients of variation in similar trials are 1.1 [14], 0.7 [15] and 0.9 [16].

Subjects will be instructed to perform a set amount of work in the shortest time possible. Total work to be performed will be calculated according to the equation of Jeukendrup, Saris, Brouns, and Kester [17], adapted based on previous experiences [12] :

Total amount of work = 0.60 · Wmax · 3,600

where Wmax is the maximal workload capacity determined at Visit 1 and 3,600 is the duration in seconds (equivalent to 1 hr). The ergometer will be set in linear mode so that 60% Wmax will be obtained when the participants cycle at their preferred cadence, which had been determined during Visit 1. The ergometer will be connected to a computer that calculates and displays the total amount of work performed. The only information participants receive is the absolute amount of work performed and the percentage of work performed relative to the set amount of work. This information will be displayed on a computer screen in front of the ergometer. A fan will be placed 1 m behind each participant to provide cooling and air circulation during the trials. The rating of perceived exertion (RPE) will be recorded at the start and when the time trial is completed, and heart rate (Polar, Finland) will be recorded continuously throughout the test. During none of the time trials, interaction will occur between the participant and the investigators except for Borg-scale recording. No encouragement will be given to the participants, and they will be kept unaware of performance-related information such as exercise time, heart rate, and cycling cadence.

Breath gas analysis will be performed during the steady state exercise for 5 minutes before every blood draw (15, 30, 45, 60 min) by indirect calorimetry with an OmniCal IV. Water will be provided during exercise ad libitum. 8 Blood samples (8ml) will subsequently be taken from an antecubital vein at t=0, 15, 30, 45, 60 and directly after completion of the time-trial.

***
[figure not shown]
***

**Figure 1: Outline of study protocol.**

# STUDY POPULATION

## Population

We want to study trained, male cyclists to examine the effects of astaxanthin supplementation on performance and fat oxidation. All subjects have to be involved in regular cycling (competition), because this increases the reliability of a time trial performance [17] .We only include male athletes, because hormonal fluctuations in female athletes might influence their performance.

## Inclusion criteria

- Healthy
- Male
- Age between 18 and 30 years
- Endurance trained (≥3 sessions of endurance exercise per week)
- VO2 max ≥ 50 ml/kg/min
- Training history of more than one year of ≥3 sessions of endurance exercise per week
- BMI <25 kg/m2

## Exclusion criteria

- Use of medication
- Smoking

## Sample size calculation

A power calculation was performed with performance as primary outcome measure. With two independent groups, the sample size (N) was calculated with a power of 80% and a significance level of 0.05 with the following formula:

z 0.8 = 0.84

z 0.975 = 1.96

Based on previous data [12, 14-17], we expect the standard deviation of performance to be about 1.3% in both groups. An improvement of 60 seconds on the time trial is considered to be a worthwhile improvement, which corresponds to 1.7% .The calculated sample size then follows to be:

Taking into consideration a drop-out rate of 20%, the final number of subjects that should be recruited per group is 12. Since we include 2 groups the total amount of subjects that need to be recruited will be 24.

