## Replacement of individual subjects after withdrawal

In case of withdrawal, the subject will not be replaced. Power calculations are based on a drop-out rate of 20%.

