# STATISTICAL ANALYSIS

## Descriptive statistics

All data will be presented as means ± SEM. Statistical analysis of the data of performance will be performed using a repeated measures anova with time (pre-post) and treatment (astaxanthin vs placebo) as factors. Likewise, differences between treatments in plasma insulin, plasma glucose, plasma FFA, plasma astaxanthine, and whole-body fat oxidation following the intervention will be analysed with 2-way repeated measures ANOVA, with time as within-subjects factor, and treatment as between-subjects factor. Statistical significance will be set at P<0.05. Data will be analyzed with SPSS 15.0 (SPSS inc, USA).

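### The sample size uses normal quantiles, but the planned ANOVA is a t-type test: power at the expected 19 or so completers is about 76–77%, not 80%

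*Protocol*

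**What the plan says.** Protocol section 4.4 (Sample size calculation) plans a comparison of two independent groups on time-trial performance: "the sample size (N) was calculated with a power of 80% and a significance level of 0.05". It lists the quantiles 0.84 and 1.96, so the test is two-sided and the formula is the normal one. On variability it says "we expect the standard deviation of performance to be about 1.3% in both groups". On the effect it says "An improvement of 60 seconds on the time trial is considered to be a worthwhile improvement, which corresponds to 1.7" percent. The recruitment target follows: "Taking into consideration a drop-out rate of 20%, the final number of subjects that should be recruited per group is 12", and then "Since we include 2 groups the total amount of subjects that need to be recruited will be 24".

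Section 6.5 (Replacement of individual subjects after withdrawal) adds: "In case of withdrawal, the subject will not be replaced. Power calculations are based on a drop-out rate of 20" percent.

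Section 8.1 names the primary analysis: "Statistical analysis of the data of performance will be performed using a repeated measures anova with time (pre-post) and treatment (astaxanthin vs placebo) as factors".

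The printed formula and the number per group before drop-out are not legible in the text available, so the order in which rounding and the drop-out allowance were applied cannot be seen.

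**The concern.** A sample size from normal quantiles treats the SD as known. The planned ANOVA estimates it from the data. With fewer than 20 degrees of freedom this costs several points of power, and in a trial of 24 subjects that is enough to fall below the stated target. Because withdrawals are not replaced, nothing in the plan makes up the difference.

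What is at stake is how the primary result is read. If the trial shows no clear difference, readers will judge that against a claimed 80% chance of detecting a 60 s improvement. If the real chance is lower under the plan's own assumptions, a null result will look somewhat more informative than it is.

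**Working it through.** **Inputs** (Protocol section 4.4 unless noted): two-sided alpha 0.05 (z = 1.96); power 80% (z = 0.84); SD 1.3% in each group; difference 1.7%, given as 60 s; drop-out 20%; 12 recruited per group; no replacement (section 6.5). A time trial of about one hour, 3,600 s (section 3), gives 60/3600 = 1.667%, which the protocol rounds to 1.7%.

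**Step 1: the plan's own figure.** For two independent means with normal quantiles:

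n = 2 × (1.96 + 0.84)² × (1.3/1.7)² = 2 × 7.84 × 0.5848 = 9.17 per group

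9.17 / 0.8 = 11.46, rounded up to 12.

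With 1.667% in place of 1.7%, n = 9.54 and 9.54 / 0.8 = 11.92, again 12. The stated 12 per group is reproduced.

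**Step 2: expected completers.** 12 × 0.8 = 9.6 per group, or 19.2 in total, about 19. In whole subjects the nearest split is 9 and 10.

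**Step 3: power by the plan's method.** At 9.6 per group the normal formula gives 81.7% (80.2% with 1.667%). On that method the 80% is met.

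**Step 4: power of the planned test.** With two time points, the time-by-treatment interaction in the repeated measures ANOVA is the same test as a two-sample t-test on the pre–post change, with n₁ + n₂ − 2 error degrees of freedom. Power comes from the noncentral t distribution with noncentrality

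λ = difference / (SD × √(1/n₁ + 1/n₂)).

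For 9 and 10 completers: λ = 1.7 / (1.3 × √(1/9 + 1/10)) = 2.846, 17 degrees of freedom, critical t = 2.110, power 76.5%.

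| Completers per group | Power, difference 1.7% | Power, difference 1.667% |
|---|---|---|
| 9 and 9 | 74.0% | 72.4% |
| 9 and 10 | 76.5% | 74.9% |
| 9.6 and 9.6 (expected value) | 77.1% | 75.5% |
| 10 and 10 | 79.0% | 77.4% |
| 11 and 11 | 83.1% | 81.6% |

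Averaged over binomial 20% loss from 12 + 12, power is 76.2% (74.6% with 1.667%).

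**Step 5: what 80% corresponds to.** Eleven completers per group is the smallest equal group size that reaches 80% by the t distribution. 11 / 0.8 = 13.75, so 14 recruited per group, 28 in total. Averaged over binomial loss, 14 per group gives 83.0% (81.6% with 1.667%), and 13 per group gives 79.9% (78.3%).

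**The case against.** The strongest reply is that the protocol is consistent with itself. It shows its normal quantiles openly, the formula is in common use, 12 per group follows from it, and at 9.6 completers that formula returns slightly more than 80%. All of this stands.

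A reader might infer a mistake in the drop-out allowance: the formula rounds up to 10, 10 / 0.8 = 12.5 calls for 13, and 12 looks like 10 × 1.2. The document does not support that inference. Rounding once, at the end, with the correct divisor gives the printed 12, and the intermediate number is not visible. Nor does the formula need 10 in a sense that 9.6 fails: it needs 9.17 (or 9.54), and 10 is only the next whole number.

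A reader might also quote 74% as the power. That figure belongs to 9 completers in each group, and losing 3 of 12 is 25%, not the planned 20%.

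Finally, the shortfall is small against the precision of the inputs. The SD is given only as about 1.3%. At 9.6 per group and a difference of 1.7%, t-test power is 80.2% with an SD of 1.25% and 74.6% with 1.34%. This limits the weight of the point, but does not remove it: at the SD the protocol chose, the planned test falls short of the stated power.

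**Conclusion.** The point holds in a limited form. At the protocol's own SD, difference and drop-out rate, the planned primary analysis has about 76–77% power at the expected completers, or about 75% if 60 s is taken as 1.667%, against the stated 80%. The whole gap, 3 to 5 percentage points, comes from using normal rather than t quantiles. No arithmetic error in the recruitment figure is shown.

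The result assumes that loss is close to 20% and roughly even between groups, that the analysis uses completers, and that 1.3% is the SD of the quantity compared, namely the pre–post change. Section 4.4 calls it only the SD of performance. Whether it is the right SD for the change is a separate question, not tested here. The severity is minor.

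**What to change.** In section 4.4, restate the claim along these lines: 24 recruited, with about 19 expected to complete, gives about 76% power (two-sided t-test at 5%) for a 60 s difference, if the SD of the change is 1.3%. If 80% is to remain the claim, the matching figure by the t distribution is 11 completers, hence 14 recruited, per group.

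Section 6.5 needs no change: it repeats the 20% drop-out rate and excludes replacement, and both agree with section 4.4.

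Restating the power costs one sentence and lowers the claim by a few points, with no change to the design. Keeping 80% would cost four more subjects in total (28 instead of 24).

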# TREATMENT OF SUBJECTS

## Investigational product/treatment

### Supplements

Subjects will be provided with either astaxanthin or placebo supplements. Subjects have to ingest 2 capsules of 4 mg with breakfast and 3 capsules with dinner throughout the 4 wk intervention period, to ascertain an intake of 20 mg/day. Astaxanthin has been shown to be safe in both animals [18] and humans [19, 20], and has recently received GRAS (generally recognized as safe) status by the US Food and Drug Administration [21]. This document also gives an excellent overview of all toxicological studies that have been performed (see attached file). Astaxanthin is produced by BioReal (Sweden). A certificate of safety for human consumption is attached.

The astaxanthin pills contain an algae extract high in astaxanthin, dissolved in sunflower oil in gelatine capsules (see attached file). The placebo treatment will consist of sunflower oil in gelatine capsules, without the astaxanthin. Treatments will look and taste identical. An independent person will randomly assign the subjects to a treatment so that both the subjects and the investigators involved in the study will be blinded to the treatment.

Astaxanthin or placebo pills have to be taken with meals (breakfast and dinner) twice daily. Astaxanthin and placebo pills will be send directly to the investigator. The supplements will be stored in a locked cabinet at room temperature, until the pills will be provided to the subjects. Compliance will be determined by the amount of pills that are left after the 4 week supplementation protocol.

# METHODS

## Study parameters/endpoints

The following parameters will be of interest for this study.

### Main study parameter/endpoint

Performance on the bicycle time trial will be the primary endpoint. The performance will be measured by the time it takes for the subject to complete a predetermined amount of work.;

### Secondary study parameters/endpoints

Fat oxidation at rest and during exercise. Blood measurements of glucose, lactate, free fatty acids, astaxanthin and cardiac troponin T.

### Other study parameters

Baseline values: VO2 max, Wmax, length, body weight, age, BMI.

## Randomisation, blinding and treatment allocation

Treatments will look and taste identical. An independent investigator will randomly assign the subjects to a treatment so that both the subjects and the investigators involved in the study will be blinded to the treatment. Randomization will be performed by a random number generator (www.random.org).

## Study procedures

### Pretesting

Body weight will be measured with a digital balance with an accuracy of 0.001 kg (E1200, August Sauter GmbH, Albstadt, Germany).

All subjects will participate in a cycling test (trial 1) to determine maximal oxygen uptake (VO2 max) and maximal workload capacity (Wmax). After a 5 min warm-up at 100 W, workload will be set at 150 W and will be increased with 50 W every 2.5 min until exhaustion [22]. O2 uptake and CO2 excretion, workload (W), cadence (rpm) and heart rate (Polar, Finland) will be recorded at every interval. The appropriate seat position, handle bar height and orientation will be determined and replicated in each subsequent visit. A familiarization trial (trial 2) will be performed to reduce learning effect over the pre and post exercise tests. The familiarization trial is identical to trials 3 and 4 (see paragraph 3.1: “protocol”)

### Diet and activity prior to test

Subjects will keep a 2-day food and physical activity diary. All subjects will be instructed to refrain from any sort of heavy physical labour. Subjects will receive a copy of their food diary and will be asked to replicate the food intake before subsequent visits. Additionally, all subjects will receive a standardized diet for the evening before the test, consisting of 55 En% carbohydrate, 15 En% protein and 30 En% fat. Subjects are allowed to eat ad libitum from the meal provided (frozen meal: Aviko familieschotel, 800g). The meal will be provided in insulated bags to keep the meal frozen during transport. Subjects will report fasted at the university for the performance tests. Subjects will be provided with a copy of their food diary. The nutritional intake the 2 days before trial 2 has to be replicated in the subsequent visits.

During the 4 week supplementation protocol, subjects are asked to refrain from eating salmon, shrimps, crab and lobster. Subjects will be asked to remain their habitual food intake and activity level during the 4 week intervention. Subjects are not allowed to take other supplements. If a subject does not comply to the guidelines, exclusion will be considered based on the type of supplement or severity of the violation of the guidelines.

### Protocol

An outline of the study protocol is provided at page 7 of this document and in figure 1 (page 9).

### Analysis

A total of 6 blood samples (8 ml) in trial 2, 3 and 4 will be collected in EDTA containing tubes and centrifuged at 1000 g and 4°C for 10 min. Aliquots of plasma will be frozen in liquid nitrogen and stored at –80°C until analysis. Glucose (Uni Kit III, Roche, Basel, Switzerland) and insulin will be analysed by radio immunoassay (Linco, Human Insulin RIA kit). Plasma free fatty acid concentrations will be analyzed with the NEFA C test kit from Wako Chemicals (Neuss, Germany). Astaxanthin content in plasma will be analyzed by reverse phase HPLC (Alliance 2690, Waters, Milford, MA). Breath gas analysis will be performed with an Omnical gas analyzer. Cardiac Troponin T will be measured by using the high-sensitivity cTnT assay on the Elecsys 2010 (Roche Diagnostics).

## Withdrawal of individual subjects

Subjects can leave the study at any time for any reason if they wish to do so without any consequences. The investigator can decide to withdraw a subject from the study for urgent medical reasons.

